## Abstract

**Background:**

The common cold is a common and frequent respiratory disease mainly caused by viral infection of the upper respiratory tract. Chinese herbal medicine has been increasingly prescribed to treat the common cold; however, there is a lack of evidence to support the wide utility of this regimen. This protocol describes an ongoing phase II randomized controlled clinical trial, based on the theory of traditional Chinese medicine (TCM), with the objective of evaluating the efficacy and safety of Lian-Ju-Gan-Mao capsules (LJGMC), a Chinese patent medicine, compared with placebo in patients suffering from the common cold with wind-heat syndrome (CCWHS).

**Methods/design:**

This is a multicenter, randomized, double-blind, placebo-controlled phase II clinical trial. A total of 240 patients will be recruited and randomly assigned to a high-dose group, medium-dose group, low-dose group, and placebo-matched group in a 1:1:1:1 ratio. The treatment course is 3 consecutive days, with a 5-day follow-up. The primary outcome is time to all symptoms’ clearance. Secondary outcomes include time to the disappearance of primary symptoms and each secondary symptom, time to fever relief, time to fever clearance, and change in TCM symptom and sign scores.

**Discussion:**

This trial is a well-designed study according to principles and regulations issued by the China Food and Drug Administration (CFDA). The results will provide high-quality evidence on the efficacy and safety of LJGMC in treating CCWHS and help to optimize the dose for the next phase III clinical trial. Moreover, the protocol presents a detailed and practical methodology for future clinical trials of drugs developed based on TCM.

**Trial registration:**

Chinese Clinical Trial Registry, ChiCTR-IPR-15006504. Registered on 4 June 2015.

**Electronic supplementary material:**

The online version of this article (doi:10.1186/s13063-016-1747-9) contains supplementary material, which is available to authorized users.

## Background

The common cold, a conventional term for a mild upper respiratory tract infection (URTI), is a common and frequent respiratory disease mainly caused by a virus [1, 2]. Adults may have about two to four episodes annually, whereas children may experience up to six to eight colds per year [2, 3]. Although the common cold is usually mild and self-limiting, with a mean duration of 7–10 days [3, 4], its economic burden on society is significant in terms of visits to health care providers, treatments, and absences from work and school [5, 6]. Besides, in some cases, viral pathogens may spread to adjacent organs, resulting in different clinical manifestations, and, occasionally, colds predispose to bacterial complications [7].

Symptoms of a cold often include fever, headache, fatigue, nasal stuffiness and discharge, sneezing, sore throat, and cough [4]. Although great progression has been achieved in Western medicine, there are still no clinically proven “gold standard” medications directly targeting the causative pathogen for treating a cold. Current treatments are limited to symptomatic supportive options that maximize the comfort of patients by reducing symptom severity and limiting the occurrence of complications; these treatments include antihistamines, decongestants, expectorants, antitussives, antipyretics, and analgesics. However, a series of adverse reactions to these drugs, such as drowsiness, dizziness, dry mouth, digestive system dysfunction, and epistaxis, occasionally occur [8–10]. Accordingly, Chinese herbal medicine as well as zinc and/or vitamin C, garlic, echinacea and vitamin D_3_, as complementary and alternative therapies, have been developed and used in patients with the common cold [11–15].

Traditional Chinese medicine (TCM) is a unique, well-established system of medicine with a history of several thousand years, which has been proven effective in the treatment of many diseases, especially the common cold. As the most important component of TCM, Chinese herbal medicine mainly derives from plants and usually incorporates one or more herbs to treat diseases. The common cold can be divided into wind-cold, wind-heat, or summer-heat and dampness syndromes according to its TCM symptoms and signs, such as fever, aversion to cold, tongue proper, tongue coating, and condition of the pulse [16], which is called syndrome differentiation (*bian zheng lun zhi*). Common cold with wind-heat syndrome (CCWHS) is the most common type and is primarily characterized by fever, mild aversion to cold, sore throat, red tongue, thin yellow tongue coating, and a floating and fast pulse.

Lian-Ju-Gan-Mao capsules (LJGMC) are a novel Chinese patent medicine, manufactured by Tasly Pharmaceutical Co., Ltd. (Tianjin, China), composed of *Yangerju (Inula cappa)*, *Chuanxinlian (herba andrographis)*, and *Shengshigao (Gypsum)* (Table 1). The drug prescription has been used as a decoction in clinical practice for years in Southwest Guizhou Autonomous Prefecture Hospital of TCM, and it has demonstrated notable efficacy in lowering body temperature, improving patients’ symptoms, and shortening the duration of the cold, with few side effects. Preclinical pharmacological and toxicological studies on animals showed that LJGMC was effective in clearing heat, relieving pain, reducing inflammation, and alleviating cough, as well as producing antiallergic, antibacterial, and antiviral effects with no evidence of toxic effects [17–20].

**Table 1 Tab1:** Pharmacological effects of each ingredient in a Lian-Ju-Gan-Mao capsule

Ingredient	Latin name	Pharmacological effects based on TCM
Yangerju	Inula cappa	Dispels wind heat, removes toxicity, and soothes throat
Chuanxinlian	Herba andrographis	Clears heat and toxicity
Shengshigao	Gypsum	Clears heat and purges lungs

*TCM* Traditional Chinese medicine

This phase II clinical trial is well designed to evaluate the efficacy and safety of LJGMC compared with placebo in patients with CCWHS. Additionally, it is expected to find a dose-efficacy relationship and to help determine the optimum dose for the next phase III clinical trial. Moreover, the protocol presents a detailed and practical methodology for future clinical trials of patent drugs developed based on TCM.

## Methods/design

### Study design

This study is a multicenter, parallel group, double-blind, prospective, randomized, placebo-controlled phase II clinical trial. A total of 240 patients will be recruited and randomly allocated into treatment groups or placebo group. All patients will receive the treatment for 3 consecutive days, with a 5-day follow-up. Efficacy and safety data will be collected throughout the whole study. The flow chart is shown in Fig. 1.

**Fig. 1 Fig1:**
[figure not shown]
Study flow chart. *AE* adverse event, *SAE* serious adverse event

### Ethics

This trial has been authorized by the China Food and Drug Administration (CFDA) (Approval Number 2012 L01822) and registered in the Chinese Clinical Trial Registry (ChiCTR-IPR-15006504). In addition, the study will be conducted in compliance with the Declaration of Helsinki, Good Clinical Practice (GCP) guidelines, and the laws and regulations of clinical trials issued by the CFDA. The protocol, informed consent form, and recruitment poster were reviewed and approved by the West China Hospital of Sichuan University Clinical Trials and Biomedical Ethics Committee (number TCM-2015-03) and the ethics committees of the other six hospitals. The investigators in all seven trial centers are qualified and well trained. All eligible participants will be fully informed about the protocol and will sign an informed consent form prior to participation. The privacy and data of all participants will be protected, and their safety will be greatly guaranteed.

### Participants and recruitment

We will recruit eligible participants by advertising on hospital notice boards, sending leaflets, or being recommended by doctors in outpatient clinics. A total of 240 patients will be recruited at the following seven hospitals: (1) West China Hospital of Sichuan University, (2) Shuguang Hospital Affiliated to Shanghai University of TCM, (3) First Affiliated Hospital of Guiyang College of TCM, 4) First Affiliated Hospital of Tianjin University of TCM, (5) Second Affiliated Hospital of Tianjin University of TCM, (6) Ruikang Hospital Affiliated to Guangxi University of TCM, and (7) First Affiliated Hospital of Guangzhou University of TCM. Forty patients will be recruited at each of the first two centers and 32 at each of the latter ones.

#### Inclusion criteria

For inclusion, participants should fulfill all the following criteria:Diagnosis of common cold according to Western medicineDiagnosis of common cold with wind-heat syndrome according to TCMAged between 18 and 65Presenting within 36 hours after symptoms onsetWillingness to participate and to sign the informed consent form.

#### Exclusion criteria

Participants with any of the following conditions will be excluded:Patients with acute herpetic pharyngitis, acute viral pharyngitis, acute herpetic laryngitis, acute viral laryngitis, acute conjunctivitis or acute tonsillitis, pneumonia, and other diseasesPatients with severe primary diseases of cardiovascular, lung, kidney, or hematopoietic system or abnormal electrocardiogram with clinical significancePatients with liver function (such as alanine aminotransferase [ALT] and aspartate aminotransferase [AST]) 1.5 times higher than the normal upper limit, abnormal serum creatinine, positive urine protein qualitative test, white blood cell count <3.0 × 10^9^/L or >10.0 × 10^9^/L, and/or neutrophil percentage >80%Patients who had used other drugs to treat common cold after the onset of the diseaseTemperature ≥39.0 °CWomen who are pregnant or preparing to become pregnant or breast feeding womenAllergic condition or allergy to the drug composition(s)Patients with mental or legal disabilitiesPatients who participated in clinical trials of other drugs within the past 3 monthsPatients who are not suitable for the trial as decided by the researchers.

#### Withdrawal criteria

The withdrawal criteria include the following:Worsening conditions during the trial, including no body temperature decline, a rising body temperature higher than 39.0 °C, or worsening symptoms in 48 hoursExperiencing anaphylaxis or serious adverse events during the trialThe study drug is not taken as required, or is taken at doses <80% or >120% of the requirementQuitting the clinical trial voluntarily.

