### Interventions

LJGMC and the placebo are provided and manufactured by Tasly Pharmaceutical Co., Ltd. (Tianjin, China). Each LJGMC or placebo weighs 0.28 g. The production batch number is 20150101. All the drugs are packaged uniformly with the same labels. Each package, which contains 3 plus 1 days’ dosage, must be sealed and kept in a cool, dry place. The placebo, which contains no effective ingredients to treat the common cold, is almost identical to the study drug in appearance, smell, and taste. A clearly visible label on each package states “FOR TRIAL USE ONLY” and other information: name, dose, dosing schedule, indication of storage condition, expiration date, and the manufacturer’s name. An independent drug manager in each center is in charge of receiving, handling, storing, and dispensing the drugs.

Patients in the high-dose group, medium-dose group, low-dose group, or placebo-matched group will receive, respectively, 1.12 g LJGMC, 0.56 g LJGMC plus 0.56 g placebo, 0.28 g LJGMC plus 0.84 g placebo, or 1.12 g placebo each time, three times per day. All medications will be taken orally with 200 ml warm water. The treatment duration is 3 consecutive days, with a 5-day follow-up. During the study, patients will be visited four times by the investigators. Details of the study procedures are given in Table 3.

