### Concomitant treatments and forbidden drugs

Patients will be allowed to continue using medications for underlying conditions, such as hypertension or diabetes. The name, dosage, and duration of any concomitant medication must be recorded carefully in the case report form (CRF). If the body temperature of a participant rises to higher than 39.0 °C for longer than 2 hours or becomes ≥39.5 °C, physical cooling and/or paracetamol can be used to kill the fever. During the study period, any other Western or Chinese therapy or medication that may affect the study results is prohibited. Once forbidden drugs are used, the patient will be withdrawn from the study.

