### Efficacy assessment

#### Primary outcome

The primary outcome is the time to all symptoms’ clearance, which is defined as the length from study enrollment to the time when the symptoms completely disappear. Each participant will be instructed to record any change in symptoms in their patient diary.

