### Data management and statistical analysis

The Drug Clinical Research Center of Shanghai University of TCM is in charge of data statistical analysis. The data entry will be performed by two independent data administrators using the software EpiData 3.1 based on the CRFs, which should have been checked and reviewed for accuracy and consistency by the clinical research associate (CRA) and investigators. Finally, the database will be locked and analyzed under the agreement and confirmed review of the sponsor, principal investigator, and statistician.

The full analysis set (FAS), in which patients should be dosed with LJGMG or placebo at least once with clinical observation record in the study, is the primary analysis set according to the intention-to-treat (ITT) principle using the last observation carried forward (LOCF) approach for missing values. All subjects without any major protocol deviations will be included in the per-protocol set (PPS). An efficacy assessment will be carried out using the FAS and PPS. A safety evaluation will be conducted for subjects who have experienced at least one study visit and have safety data, which is defined as the safety set (SS).

All continuous and normally distributed data are presented as mean ± standard deviation, and median with range for non-normal data. Categorical data are summarized by frequency counts and percentages. Baseline balance among groups will be conducted by performing a chi-squared test or an analysis of variance (ANOVA). Time to all symptoms’ clearance, time to primary symptoms and each secondary symptom disappearance, time to fever relief, and time to fever clearance will be estimated and compared by the log-rank test. A Kaplan-Meier survival curve will be constructed, and the median time will be provided separately for each group with a two-sided 95% confidence interval. Comparisons among groups of TCM symptom and sign scores will be conducted using ANOVA and the Bonferroni method. All data will be processed by a professional statistician using SAS 9.2 software (SAS Institute, Cary, NC, USA); a two-sided *P* value of <0.05 is considered to be statistically significant.

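### The withdrawal rules tie loss of the primary outcome to response and adherence, and nothing keeps withdrawn patients under outcome follow-up, which undercuts the intention-to-treat claim

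*Protocol article*

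**What the plan says.** All references are to the protocol article.

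- **Withdrawal criteria.** The first item is "Worsening conditions during the trial, including no body temperature decline", followed by a rise above 39.0 °C or worsening symptoms, with a 48-hour window. It is not clear whether the 48 hours govern all three parts. A later item covers drug not taken as directed, or intake under 80% or over 120% of the requirement.
- **Concomitant treatments and forbidden drugs.** "Once forbidden drugs are used, the patient will be withdrawn from the study".
- **Interventions.** The placebo arm takes "1.12 g placebo each time, three times per day", and the other arms follow the same schedule. "The treatment duration is 3 consecutive days, with a 5-day follow-up".
- **Primary outcome.** It is "the length from study enrollment to the time when the symptoms completely disappear", recorded in a patient diary.
- **Data management and statistical analysis.** The full analysis set (FAS) needs at least one dose and an observation record. It "is the primary analysis set according to the intention-to-treat (ITT) principle using the last observation carried forward (LOCF) approach for missing values". The sentence that names the test starts its list with the primary outcome and ends: "time to fever clearance will be estimated and compared by the log-rank test".
- **Sample size.** Duration is taken as 7 ± 3 days, with a 2-day reduction as the target and a 20% drop-out allowance.

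No section states that diary recording or contact continues after a withdrawal criterion is met.

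**The concern.** Not improving, getting worse and reaching for another remedy are consequences of how well treatment works. If the drug has an effect, they should occur more often on placebo or on a weak dose. The 48-hour trigger acts about day 2, well before the expected clearance time of about 7 days. The rules thus tend to end observation of likely slow resolvers before their outcome is known, and probably at different rates by arm.

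A log-rank test assumes that a censored patient has the same prospects as those who remain. These rules make that assumption implausible. Last observation carried forward (LOCF) does not settle the matter, because it has no clear meaning for a time-to-event outcome.

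The trial is also meant to inform the phase III dose, so distortion that varies by arm bears on that choice as well as on the comparison with placebo. Diary data that were never collected cannot be recovered by any later analysis plan.

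**Working it through.** **1. The plan's own figure.** Inputs from the Sample size section: difference 2 days, SD 3, two-sided α = 0.05, power 90%.

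n = 2 × (1.960 + 1.282)² × 3² / 2² = 47.3, rounded up to 48 per group. Allowing for drop-out, 48 / (1 − 0.20) = 60. Both stated figures reproduce. The allowance restores numbers (48 completers give 90.4% power by the normal approximation, 89.8% by the t-test). It does nothing about which patients are lost.

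**2. The adherence threshold.** 3 doses × 3 days = 9 doses. One missed: 8/9 = 88.9%, above 80%. Two missed: 7/9 = 77.8%, below 80%.

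**3. Effect of censoring at withdrawal.** Durations N(7, 3) on placebo and N(5, 3) on active; observation 3 + 5 = 8 days. *Assumption:* half of the patients not cleared by day 8 are withdrawn at day 2.

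| | Placebo | Active |
|---|---|---|
| Cleared by day 2 | Φ(−5/3) = 4.8% | Φ(−1) = 15.9% |
| Not cleared by day 8 | 1 − Φ(1/3) = 36.9% | 1 − Φ(1) = 15.9% |
| Withdrawn (half of these) | 18.5% | 7.9% |
| True day-8 clearance | 63.1% | 84.1% |
| Expected Kaplan-Meier clearance, withdrawn censored | 1 − 0.952 × 0.185/(0.952 − 0.185) = 77% | 1 − 0.841 × 0.079/(0.841 − 0.079) = 91% |

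The difference falls from 21 to 14 percentage points. In simulation at 60 per arm, log-rank power is about 91% with full follow-up. If 30%, 50% or 80% of those not cleared by day 8 are withdrawn and censored, it is about 86–87%, 81–82% and 68–72% (ranges over repeated runs). If the same patients are carried forward as not cleared, power stays at about 90–91%, because by construction none of them would have cleared by day 8.

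**4. A looser link between withdrawal and duration.** Gamma durations with SD 3, 60 per arm, 1,000 runs per scenario. Withdrawal at day 2 is weighted towards slow resolvers but not confined to them. The entries are two-sided rejection rates.

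| Means, placebo/active (days) | Withdrawn, placebo/active (assumed) | Full follow-up | Censored | Carried forward as not cleared |
|---|---|---|---|---|
| 7 / 5 | 20% / 10% | 92% | 85% | 94% |
| 7 / 5 | 30% / 10% | 92% | 74% | 98% |
| 7 / 7 | 20% / 10% | 4.6% | 7.8% (mostly against the drug) | 4.6% (mostly for the drug) |
| 7 / 7 | 30% / 10% | 5.9% | 17% (16.5% against the drug) | 10% (almost all for the drug) |
| 7 / 7 | 20% / 20% | 4.5% | 6.1% | 1.9% |

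The two ways of handling the same patients pull in opposite directions. With no effect on duration, error is not materially inflated when withdrawal is equal across arms.

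**The case against.** The strongest reply is that the article condenses a fuller protocol, so handling after withdrawal may be set out elsewhere. That stands for censoring rules and similar detail. It does not dispose of the point, because the withdrawal rules are stated conduct rules and one of them expressly removes the patient from the study.

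Several stronger readings are tempting, and the document does not support them:

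- *All three triggers remove the patient from the study.* Only the forbidden-drug rule says so. The Withdrawal criteria section does not distinguish stopping drug from stopping follow-up. Serious adverse events are on that list, yet the Safety evaluation section leaves study withdrawal after such an event to a decision, so the list is not plainly automatic exit.
- *Withdrawn patients drop out of the primary analysis.* They were dosed and observed, so they remain in the FAS and in their arm. What fails is follow-up irrespective of response and adherence.
- *The trial will lose power.* That needs censoring at withdrawal, which is not stated. LOCF could be read as carrying the patient forward as not cleared, and then the loss of power does not arise.
- *The power figures predict this trial.* The day-8 scenario removes only patients who would not have cleared by then. The actual triggers concern temperature and early worsening, while the outcome also includes cough and nasal symptoms. If 18% and 8% withdraw for reasons unrelated to duration, power is 88% even with censoring.
- *The dosing rule loses the fastest recoverers.* A patient who clears on day 2 and then stops capsules already has the primary event. Exclusion from the per-protocol set is an inference, since major deviations are not listed.

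**Conclusion.** The concern holds in this form: stated rules make loss of the primary outcome depend on response and adherence, no section preserves follow-up, and the intention-to-treat label is undercut for that reason. The adherence arithmetic follows directly from the protocol's dosing schedule.

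The size and direction of bias are conditional. Under assumed withdrawal rates, censoring costs roughly 9 points of power when half of the slow resolvers are withdrawn (91% to 82%). Under no effect with 30% against 10% withdrawn, it raises rejection to about 17%, almost all against the drug. Carrying patients forward as not cleared gives about 10% in the same null scenario, almost all for the drug. The protocol gives no withdrawal rates by arm and does not fix the handling, so no single bias figure can be attached to it.

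Separately, the Withdrawal criteria section lists a temperature above 39.0 °C as grounds for withdrawal. The section on concomitant treatments permits cooling or paracetamol when the temperature stays above 39.0 °C for longer than 2 hours or reaches 39.5 °C. The two sections must be reconciled.

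**What to change.** 1. In the Withdrawal criteria section and the section on forbidden drugs, separate stopping study drug from leaving the study. The clinical triggers themselves need not change for this.
2. State that every dosed patient who has not withdrawn consent continues the symptom diary and contact to the end of the 5-day follow-up (day 8).
3. Analyse observed clearance times in the FAS by log-rank, regardless of discontinuation or forbidden-drug use. Remove LOCF for the time-to-event outcomes.
4. Report two sensitivity analyses: discontinued patients counted as not cleared to day 8, and patients censored at discontinuation. Since these err in opposite directions, neither should be the sole primary rule.
5. Reconcile the two sections on temperature above 39.0 °C.

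The cost is a protocol amendment, a few more diary days from patients already in contact, and a flag for data after discontinuation. The estimate will then include any effect of other remedies taken after study drug stops. The article reports that recruitment is under way, so the change protects only patients still within follow-up or yet to enter.
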